### Strategies to improve adherence to interventions

The following strategies are used to increase adherence to the exercise program. (1) The exercise program is designed to be done at home, moving away from supervised sessions, to be more in context with natural living conditions; (2) the exercise program components are designed to be completed either in one session or split sessions; (3) the exercise program was designed to minimize injuries/soreness by beginning light-moderate and increasing over time; (4) the exercise program contains a self-monitoring Exercise Diary in REDCap and weekly telephone follow-ups to provide coaching regarding exercise-related issues and encourage completion of the Exercise Diary throughout the study period.

### Relevant concomitant care permitted or prohibited during the trial

Participants in the attention control group agree not to begin a new exercise program or change their level of exercise during the study.

### Outcomes

The primary outcome is to assess the effects of exercise on gait, balance, and lower extremity muscle strength in 312 women randomized to either a 16-week home-based gait/balance intervention or an attention control educational cancer survivorship condition. The gait assessment includes spatiotemporal metrics (cadence, speed, foot strike angle, stance percent, stride length, and swing percent) and lower extremity joint kinematics (hip, knee, and ankle joint angles). The APDM Opal (Mobility lab v1, APDM, Inc., Portland, OR) inertial measurement units (IMU) system assesses gait. The APDM IMUs are wireless sensors for measuring motion that allows clinicians to perform gait assessments quickly and straightforwardly [17, 18]. Balance is assessed using the Sensory Organization Test (SOT) performed using a NeuroCom Balance Master (NeuroCom International Inc, Clackamas, OR) and the EquitTest System (v8.0). The SOT measures the participants’ ability to effectively use visual, vestibular, and somatosensory information to maintain balance. The SOT equilibrium score has demonstrated moderate to excellent test-retest reliability in healthy older adults and individuals with Parkinson’s disease [19–21]. Isometric strength of hip, knee, and ankle flexor and extensor muscles is assessed using an isokinetic dynamometer, Biodex BX Advantage (Biodex Medical Systems, Shirley, NY, USA), and the computer software program version 3.29 and 3.30 [22–25]. We also assess neuropathy symptoms using the FACT-Taxane Additional Concerns Subscale and nerve conduction velocity of the sural and peroneal nerve action potentials [26, 27]. Different outcomes will be analyzed separately. Multiple comparison methods such as the Bonferroni-Holm Method will be applied to control family-wise error rates.

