#### SEM approach

The variance population parameters recommended by Muthén and Muthén were used (intercept variance = 0.50, slope variances (intervention = 0.10, intercept and slope covariances = 0.00), and residual variance at all waves = 0.50). Homogeneity of variances was assumed between the treatment and control groups. To reflect effective randomization of participants to conditions, we modeled no mean difference between treatment and control conditions at baseline. The differences in slopes between the treatment and control conditions during the intervention period are the focal parameter to be adequately powered. Given alpha = .05, a two-tailed hypothesis test, and the view that a power value of .80 will be adequate to detect a treatment effect, a minimum sample of *N* = 312 participants (based on recruitment of 2 or more participants per week for 3 years) with 20% attrition and 10% periodic non-response, is needed.

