#### Intention to treat (ITT) approach

A full-information maximum likelihood approach for an intent-to-treat analysis is used, and a Monte Carlo simulation with 10,000 replications suggests we will be able to detect a minimum standardized effect of 0.30 with a probability of correctly rejecting a false null (power) of .81. If the recruitment rate is closer to 3 per week resulting in a sample of *N* = 468, the minimum detectable standardized effect is 0.25. By including additional control variables (all ES’s = .10), the minimum detectable effect sizes decrease to 0.27 and 0.22, respectively. A recent and relevant meta-analysis reported effect sizes for exercise intervention effects on similar outcomes ranging from ES = 0.30 to ES = 0.84 [30]. We will compare the mean differences between groups and the rates of change (slopes) between the groups.

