The assessment of gait includes six spatiotemporal parameters: cadence [steps/min], speed [m/s], foot strike angle [degrees], stance percent [% of gait cycle time GCT], stride length [m], and swing percent [% of GCT]. In addition, the assessment of gait includes the sagittal plane kinematics (range of motion ROM) of three lower extremity joints: hip flexion-extension ROM [degrees], knee flexion-extension ROM [degrees], and ankle dorsiflexion-plantarflexion ROM [degrees]. Preprocessing of raw data and extraction of spatiotemporal gait variables and joint ROM are performed using APDM’s mobility lab software (Version 1). The mobility lab software computes the mean and standard deviation for each gait outcome variable from approximately 50–60 gait cycles collected during gait assessment. After testing, the mobility lab software automatically generates a report in CSV format containing the mean and standard deviation for each outcome variable. The CSV files are then imported to the REDCap database for further statistical analysis.

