### Assessment of lower extremity muscle strength

Isometric strength of hip, knee, and ankle flexor and extensor muscles is assessed using an isokinetic dynamometer, Biodex BX Advantage (Biodex Medical Systems, Shirley, NY, USA), and the computer software program version 3.29 and 3.30. The test protocols have been established based on the Biodex BX Advantage manual and recommendations from other studies [22–25]. The dominant and non-dominant legs are tested. Before each test, participants will become familiar with the procedures by performing 2–3 contractions as warm-ups. During the test, participants are guided with standardized instructions during the test to encourage sub-maximal muscle performance. Participants are stabilized in the chair with shoulder and abdominal straps. The anatomical axis of rotation is aligned to the dynamometer axis using visual inspection and manual palpation. The isometric tests include three sets of sub-maximal muscle contractions, each set lasting 5 s separated by 10 s rest intervals. The isometric strength of the hip muscles is assessed with subjects in a supine position with the hip joint positioned at 45° of flexion [22]. For assessment of the knee muscles, subjects are positioned in sited position with the knee positioned at 60° of flexion [36, 37]. To evaluate the ankle muscles, subjects are positioned in a sited position with the ankle joint positioned in a neutral position (0°) [38]. Participants performed three sets of isometric contractions for extensor and flexor muscles of the hip, knee, and ankle joints. The reliability of muscle strength values measured using isokinetic dynamometers is excellent [39, 40]. It has shown good to excellent reliability in healthy older adults and patients with hereditary motor sensory neuropathy [25, 41]. As shown in Table 3, the lower extremity muscle strength measures used in this study demonstrated good to excellent test-retest reliability (*r* > 0.7; ICC > 0.80) [35].

The Biodex Advantage BX 4. X Software is used to calculate the peak torque [Newton-meters, Nm] (i.e., highest force output during each sub-maximal muscle isometric contraction) and the average peak torque (i.e., average force output of a given set). The average peak torque (Newton-meters, Nm) obtained in each series is used for data analysis.

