### Data analysis

Univariate descriptive statistics will be used to describe the characteristics of the sample, gait, balance, and lower extremity muscle strength. Values for the exercise will be divided into quartiles to determine the uppermost and lowest values to compare with published literature [43]. Analysis of univariate statistics allows us to assess the normality of distributions for our continuously distributed variables, patterns of missing values, and whether univariate outliers may be present that could distort subsequent bivariate and multivariate analyses. By implementing appropriate link functions in the generalized linear model framework, distributional assumptions, such as normality and potential non-linearity, will be addressed. Potential non-normality may also be addressed by implementing robust estimation through Huber-White standard errors (i.e., “sandwich” estimators), also implementable in the generalized mixed model framework. We do not aggregate outcomes. Instead, we are looking at a specific change of each metric between baseline and 16 weeks and comparing study groups. In addition, we will perform baseline comparisons between groups. Any unbalance covariate(s) will be adjusted in multivariate analyses. We do not plan any subgroup analyses.

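### The stated power of .81 is for one test at two-sided .05, but the primary metrics are to be tested separately under family-wise error control, so it does not apply to most of the planned tests

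*Protocol article*

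**What the plan says.** The sample size section (SEM approach) powers a single quantity: "The differences in slopes between the treatment and control conditions during the intervention period are the focal parameter to be adequately powered". The test level is "Given alpha = .05, a two-tailed hypothesis test". The ITT approach paragraph gives the result for 312 participants, namely that the trial can "detect a minimum standardized effect of 0.30 with a probability of correctly rejecting a false null (power) of .81". Neither paragraph mentions an adjustment for multiple tests.

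The Outcomes section makes gait, balance and lower extremity strength jointly the primary outcome, says that different outcomes are analysed separately, and adds: "Multiple comparison methods such as the Bonferroni-Holm Method will be applied to control family-wise error rates". The Data analysis section rules out a composite ("We do not aggregate outcomes") and compares the groups on the change in each metric.

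The assessment sections supply the metrics:
- **Gait:** six spatiotemporal parameters and "the sagittal plane kinematics (range of motion ROM) of three lower extremity joints".
- **Balance:** one SOT composite equilibrium score.
- **Strength:** flexors and extensors of hip, knee and ankle, where "The dominant and non-dominant legs are tested".

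No section names a single primary variable or says which metrics form a family.

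**The concern.** A power figure is useful only if it refers to the test that will decide the question. Here it refers to one comparison at .05, while the plan commits to several separate primary comparisons at a stricter, adjusted level. A reader would take the trial to have about 80% power for its primary metrics at an effect of 0.30. Under the promised adjustment most of them have clearly less.

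The value 0.30 matters because it is both the effect the trial is sized for and the bottom of the range (0.30 to 0.84) that the protocol cites from a meta-analysis. If true effects lie near that end, non-significant results on individual metrics would be likely and could be misread as evidence of no benefit. It is also unclear what would count as a positive primary result.

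**Working it through.** **1. The plan's own figure.** The inputs from the SEM approach paragraph are intercept variance 0.50, slope variance 0.10, covariance 0 and residual variance 0.50; the design is 1:1 with 156 per arm. I assume time coded 0/1, the effect in baseline SD units, and a baseline-adjusted comparison, because the protocol does not state its scaling.
- Baseline variance: 0.50 + 0.50 = 1.00. Follow-up variance: 0.50 + 0.10 + 0.50 = 1.10. Covariance: 0.50.
- Variance given baseline: 1.10 − 0.50²/1.00 = 0.85.
- Standard error: √(0.85 × 2/156) = 0.104. Ratio: 0.30/0.104 = 2.87. Power: Φ(2.87 − 1.96) = .82.

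A 10,000-replication simulation gives .81. The stated figure is thus recovered as a single test at .05 with all 312 participants analysed. From here on I take .81 as correct.

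**2. Implied noncentrality.** z(.975) + z(.81) = 1.960 + 0.878 = 2.838.

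**3. Family size, counted from the text.**
- Gait: 6 + 3 = 9. Balance: 1. Strength: 6, or 12 if the legs are analysed separately.
- One overall family: 9 + 1 + 6 = 16, or 9 + 1 + 12 = 22.

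**4. Power at the first Holm step.** This is the power for a given metric when it is the only one that responds. Power = Φ(2.838 − z(1 − .05/(2m))). The effect detectable with 80% power = 0.30 × (z(1 − .05/(2m)) + 0.842)/2.838.

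| Family | m | .05/m | Critical z | Power at 0.30 | Detectable effect |
|---|---|---|---|---|---|
| Single test, or balance alone | 1 | .0500 | 1.960 | .81 | 0.30 |
| One variable per domain | 3 | .0167 | 2.394 | .67 | 0.34 |
| Strength, 6 metrics | 6 | .0083 | 2.638 | .58 | 0.37 |
| Gait | 9 | .0056 | 2.773 | .53 | 0.38 |
| Strength, legs separate | 12 | .0042 | 2.865 | .49 | 0.39 |
| All metrics, 6 strength | 16 | .0031 | 2.955 | .45 | 0.40 |
| All metrics, legs separate | 22 | .0023 | 3.052 | .42 | 0.41 |

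**5. Full Holm procedure.** This was simulated with 100,000 replications and equal correlations from 0 to .8. Per-metric power at 0.30 is:
- m = 16: .48-.49 if half the metrics respond, .55-.56 if all do.
- m = 22: .44-.45 if half respond, .50-.52 if all do.

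Holm rejects a hypothesis only if its unadjusted p is at most .05, so no metric can exceed the single-test .81.

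**6. Sample size equivalent.** Power .81 at 0.30 at the first step needs 312 × ((critical z + 0.878)/2.838)², about 570 for m = 16 and 599 for m = 22.

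**The case against.** **The family is not defined.** Holm is named only as an example, and the protocol speaks of error rates in the plural, so families per domain are an open reading. This stands. A reader might infer that no primary metric has the stated power, but the documents do not support that: balance has one metric and, as its own family, would be tested at .05 and keep .81. Gait and strength would still fall to about .53 and to .58 or .49 at the first step.

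**The count of 22 is a reading.** The protocol says both legs are tested, not that they are analysed separately, and its reliability table lists six strength measures. This stands, so 22 is conditional.

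**Effects may exceed 0.30.** At 0.45 the noncentrality is 2.838 × 1.5 = 4.257, and first-step power is about .90 (m = 16) or .89 (m = 22). The protocol's covariate-adjusted detectable effect of 0.27 scales to about 0.36-0.37. Both points are fair. They limit the consequence, but they do not make .81 at 0.30 correct for the adjusted tests.

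**Some metric would probably succeed.** If all metrics respond, the chance of at least one rejection is .76 to 1.00, depending on correlation. That is true, but the protocol does not say that one rejection counts as success. A reader might also infer that a real effect of 0.30 would usually be missed on a given metric. That fits only when few metrics respond, since with all responding per-metric power is .50 to .56.

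**The analysis plan may settle the family.** It may. But the level, the power and the promise of adjustment are all stated in this protocol and do not fit together there.

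**Conclusion.** The concern holds in this form: .81 is a single-test figure, and the plan's own family-wise control means it does not apply to the gait and strength metrics, nor to balance if there is one overall family. In one overall family, first-step power at 0.30 is about .45 (16 metrics) to .42 (22), and .50 to .56 per metric if every metric responds. The 80% detectable effect is about 0.40-0.41. These figures rest on accepting .81, on Holm being the method used, and on the family counts above.

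Two further inferences are not supported. First, this is not a false-positive problem: with family-wise control, each rejection is valid. Second, a reader might conclude that .81 is itself wrong, because under the assumptions in the working it is recovered only without the planned 20% attrition (with that loss it is about .73). The protocol does not give the scaling used in its simulation, so that cannot be settled here.

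**What to change.** State the primary family and the multiplicity procedure, and restate power and the detectable effect at the adjusted alpha.

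Preferably, the sponsor names one primary variable per domain before outcome data are seen. Balance already has only the SOT composite; the choice within gait and strength is the sponsor's. Apply Holm across the three and make the other metrics secondary. At 0.30, power is then about .67 if one domain responds and about .75-.76 each if all three do (simulation, correlation 0 to .3). The 80% detectable effect is about 0.34. This does not restore .80 at 0.30, and the protocol should say so.

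If the full family is kept, restate power for that family and say whether the legs are separate tests. Count stance and swing percent once: both are percentages of the same gait cycle and are complements. The gain is small (m = 15 instead of 16 gives about .46 instead of .45).

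The cost is a less favourable stated power, a protocol amendment, and the remaining metrics becoming secondary. With 33 of 312 participants recruited at protocol version 2, the change is still early.

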### Participant timeline

Table 3 shows the participant timeline.

**Table 3 Tab3:** Participant timeline

Recruitment Screening Study information	
**Baseline visit:** Informed consent Baseline assessment of gait, balance, muscle strength Neuropathy symptoms patient-reported questionnaire Nerve conduction velocity assessment Randomization	
**Home-Based Physical Activity Intervention group**	**Educational attention control group**
Week 1–week 4	Week 1–week 16
Gait/balance exercise and resistance exercises 3 days per week Exercise diary Follow-up phone call weekly	Standardized breast cancer survivorship education from American Cancer Society Follow-up phone call bi-weekly
Week 5–week 16 Gait/balance exercise and resistance exercises 3 days per week Exercise diary Follow-up phone call bi-weekly	
**End of treatment visit:** Baseline assessment of gait, balance, muscle strength Neuropathy symptoms patient-reported questionnaire Nerve conduction velocity assessment	**End of treatment visit:** Baseline assessment of gait, balance, muscle strength Neuropathy symptoms patient-reported questionnaire Nerve conduction velocity assessment

### Sample size

Power analyses were performed through a Monte Carlo simulation approach with the software Mplus [28, 29]. Observations were spaced at 0 and 16 weeks, with the number of weeks since baseline as the time metric to evaluate the efficacy of the 16-week intervention.

#### SEM approach

The variance population parameters recommended by Muthén and Muthén were used (intercept variance = 0.50, slope variances (intervention = 0.10, intercept and slope covariances = 0.00), and residual variance at all waves = 0.50). Homogeneity of variances was assumed between the treatment and control groups. To reflect effective randomization of participants to conditions, we modeled no mean difference between treatment and control conditions at baseline. The differences in slopes between the treatment and control conditions during the intervention period are the focal parameter to be adequately powered. Given alpha = .05, a two-tailed hypothesis test, and the view that a power value of .80 will be adequate to detect a treatment effect, a minimum sample of *N* = 312 participants (based on recruitment of 2 or more participants per week for 3 years) with 20% attrition and 10% periodic non-response, is needed.

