**Fig. 3 Fig3:**
[figure not shown]
APDM Opal Sensors Placement. IMUs (inertial measurement units), LC (lateral condyle), TT (tibial tuberosity), TAT (tibialis anterior tendon), SL (shoe length)

Before starting the walking assessment, participants are instructed to assume a neutral standing posture for 10 s and walk for approximately 2 min. Next, participants are instructed: “When ready, stand against this wall and place your feet in line with the tape arrows. Ensure your heels, back, and head are resting against the wall with your hands resting on your sides. Hold this position for about 10 seconds. Then, begin walking at the usual, comfortable walking speed. Next, turn and continue walking at a normal pace back and forth for 2 minutes. I will say STOP when the test is complete, then please take a seat.” During the testing, participants are instructed to “keep walking at your normal pace.” As shown in Table 4, the spatiotemporal metrics of gait (*r* > 0.86; ICC > 0.90) and gait kinematics (*r* > 0.7; ICC > 0.75) measures used in this study demonstrated excellent and good test-retest reliability, respectively [35].

**Table 4 Tab4:** Reliability of outcome measures

Reliability		*r*	ICC
Isometric strength	Hip extension (Nm)	0.74	0.85
	Hip flexion (Nm)	0.92	0.96
	Knee extension (Nm)	0.94	0.96
	Knee flexion (Nm)	0.95	0.97
	Ankle plantarflexion (Nm)	0.92	0.94
	Ankle dorsiflexion (Nm)	0.91	0.96
Gait			
Spatiotemporal metrics	Cadence (steps/min)	0.97	0.98
	Gait speed (m/s)	0.86	0.93
	Foot strike angle (degrees)	0.93	0.96
	Stance (%)	0.97	0.99
	Stride length (m)	0.95	0.98
	Swing (%)	0.97	0.99
Kinematics	Hip flexion (degrees)	0.70	0.82
	Hip extension (degrees)	0.70	0.82
	Knee flexion (degrees)	0.71	0.77
	Knee extension (degrees)	0.82	0.86
	Ankle plantarflexion (degrees)	0.94	0.95
	Ankle dorsiflexion (degrees)	0.93	0.93
Balance	Composite equilibrium score (%)	0.87	0.67

*r* Pearson’s correlation, *ICC* intraclass correlation coefficient

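### The stated detectable effect (0.30 at power 0.81 with N = 312) does not follow from the simulation inputs that the protocol gives

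*Protocol article*

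**What the plan says.** All of this is in the Protocol article.

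- **Sample size:** a Monte Carlo simulation is described "with the number of weeks since baseline as the time metric to evaluate the efficacy of the 16-week intervention". Each participant has two observations, one at baseline and one at week 16.
- **SEM approach:** the variances are generic published recommendations: intercept 0.50, slope 0.10, covariance 0.00 and "residual variance at all waves = 0.50". No baseline difference is modelled, and the difference in slopes is the parameter to be powered. The test is specified as "Given alpha = .05, a two-tailed hypothesis test", and "a power value of .80 will be adequate to detect a treatment effect". N = 312 is a recruited number (2 per week for 3 years: 2 × 52 × 3 = 312), to be reduced by 20% attrition and 10% non-response.
- **Intention to treat (ITT) approach:** the trial can "detect a minimum standardized effect of 0.30" with "probability of correctly rejecting a false null (power) of .81". With N = 468 the figure is 0.25. The SD used to standardize these effects is not given.
- **Table 4 and the assessment sections:** test-retest reliability is reported for 19 measures, with r from 0.70 to 0.97 (median 0.92). For spatiotemporal gait and kinematics, the "measures used in this study demonstrated excellent and good test-retest reliability, respectively". For strength, "the lower extremity muscle strength measures used in this study demonstrated good to excellent test-retest reliability". Balance has r 0.87 and ICC 0.67.

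**The concern.** Two features of the inputs do not look right.

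First, a slope variance multiplies the square of time. A value of 0.10 is modest if time runs from 0 to 1, but enormous if it runs from 0 to 16. Either the time scale or the slope variance is therefore misdescribed, and the published effect and power may not come from the inputs shown.

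Second, equal intercept and residual variances treat half of every outcome's baseline variance as noise. The protocol's own reliability table reports much less.

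The detectable effect is the only statement of what the trial can find. The protocol sets it against a meta-analytic range of 0.30 to 0.84 and offers N = 468 as an alternative. Trial status reports 33 participants recruited, so the target may well be revisited. A figure that cannot be regenerated from its stated inputs is a poor basis for that discussion.

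**Working it through.** **Inputs.** Intercept variance 0.50, slope variance ψ = 0.10, covariance 0, residual 0.50, waves at 0 and 16 weeks, two-sided alpha 0.05, power 0.81, N = 312 at 1:1, losses 20% then 10%. Assumption: the losses multiply, so the number with a week-16 value is n = 312 × 0.80 × 0.90 = 224.6.

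**Formulas.** With time score T at week 16:

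- Baseline variance V0 = 0.50 + 0.50 = 1.00
- Week-16 variance V16 = 0.50 + ψT² + 0.50
- Covariance C = 0.50

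In a full-information likelihood analysis with equal baseline means, the SE of the group difference at week 16 is √[4(V16 − C²/V0)/n]. Power is Φ(δ/SE − 1.96). The detectable effect at power 0.81 is (1.960 + 0.878) × SE = 2.838 × SE, divided by the standardizing SD.

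**1. Time in weeks, as written (T = 16).**

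- V16 = 1.00 + 25.6 = 26.6, so the SD is 5.16 against 1.00 at baseline. The correlation is 0.50/√26.6 = 0.10.
- SE = √[4 × 26.35/224.6] = 0.685.
- An effect of 0.30 week-16 SDs is 0.30 × 5.16 = 1.55 baseline SDs. Power = Φ(1.547/0.685 − 1.96) = 0.62. The detectable effect is 2.838 × 0.685/5.16 = 0.38.
- With no losses, power is 0.76. If 0.30 is in slope-SD units, power is 0.60. If it is in baseline SDs, power is 0.06.

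**2. Time scored 0/1 (T = 1).**

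- V16 = 1.10 and the correlation is 0.50/√1.10 = 0.48.
- SE = √[4 × 0.85/224.6] = 0.123.

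| Losses | Power at 0.30 (baseline SD to week-16 SD) | Detectable effect at 0.81 (baseline SD to week-16 SD) |
|---|---|---|
| None | 0.82 to 0.85 | 0.296 to 0.282 |
| 20% only | 0.73 to 0.77 | 0.331 to 0.316 |
| 20%, then 10% | 0.68 to 0.73 | 0.349 to 0.333 |

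If the baseline means are left free, the last row becomes 0.60 to 0.64, with a detectable effect of 0.384 to 0.366.

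**3. Reproducing 0.81.** Of the variants tried, the only one within two points is 0/1 scoring, equal baseline means, baseline SD and no losses (0.82). It leaves out the attrition that the protocol says is included.

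**4. N = 468.** Here n = 468 × 0.72 = 337. Under 0/1 scoring, power at 0.25 is 0.70 to 0.74 and the detectable effect is 0.285 to 0.272. In weeks, SE = √[4 × 26.35/337] = 0.559 and the detectable effect is 2.838 × 0.559/5.16 = 0.31.

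**5. Reliability.** The inputs imply a baseline reliability of 0.50/(0.50 + 0.50) = 0.50. Hold the baseline variance at 1, set the residual to 1 − r and score time 0/1. The term in the SE is then (1 + ψ) − r². Detectable effect at 0.81 with both losses, in baseline SDs:

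| Reliability | ψ = 0.10 | ψ = 0.30 |
|---|---|---|
| 0.50 (plan) | 0.349 | 0.388 |
| 0.67 (balance ICC) | 0.306 | 0.349 |
| 0.70 | 0.296 | 0.341 |
| 0.82 | 0.248 | 0.300 |
| 0.92 (median r) | 0.191 | 0.255 |
| 0.97 | 0.151 | 0.227 |

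Fifteen of the 19 rows have r of 0.82 or more. The other four are hip flexion and hip extension kinematics (0.70), knee flexion kinematics (0.71) and hip extension strength (0.74).

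With time in weeks, reliability hardly matters: the detectable effect is 0.377 at reliability 0.50 and 0.372 at 0.97.

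**The case against.** The best defence is that these are openly generic planning values, and that the noise assumption errs on the safe side. Most of that stands, and it rules out several stronger readings.

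- A reader might infer that 0.30 belongs to none of the primary metrics. It does not follow. With Table 4 reliability, ψ = 0.10, 0/1 scoring and the stated losses, the detectable effect is 0.28 to 0.30 at r = 0.70 to 0.74, and 0.306 for balance at its ICC. The agreement is a coincidence, because the plan used 0.50, but the number is not foreign to every metric.
- A reader might call the residual variance a contradiction of Table 4. A growth-model residual can also hold true fluctuation between occasions, so test-retest reliability informs it without fixing it. The article gives neither the sample nor the retest interval behind Table 4. The table also lists flexion and extension angles separately, whereas the gait outcome is range of motion per joint.
- A reader might infer that the 0.50 leaves the trial underpowered. Under 0/1 scoring the reverse holds: higher reliability lowers the detectable effect.
- A reader might add the two faults together. They are alternatives. The reliability question matters under 0/1 scoring and almost vanishes in weeks.

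It can also be said that the standardizing SD is unstated, so some other definition might give 0.81. That cannot be excluded, but the usual choices were tried on both codings and none gives 0.81 with the stated losses. The defence does not answer the time-scale problem: as written, the variance grows about 27-fold in 16 weeks.

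**Conclusion.** The concern holds in this form: the stated 0.30 at power 0.81 is not what the stated inputs yield. With both losses, power at 0.30 is about 0.62 in weeks (detectable effect about 0.38). Under 0/1 scoring with equal baseline means it is 0.68 to 0.73 (detectable effect about 0.33 to 0.35). The weeks reading also rests on an implausible variance structure.

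The reliability mismatch is secondary and conservative. With Table 4 r and slope variance 0.10, the detectable effect would be about 0.30 for the least reliable metrics and 0.25 or lower for 15 of 19 rows. With slope variance 0.30 it would be about 0.23 to 0.34 across r = 0.97 to 0.70.

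The documents therefore do not show that N = 312 is too small. They show that the published figure cannot be relied on in either direction. The result rests on multiplicative losses, on a two-wave analytic calculation in place of the simulation, and on the usual definitions of a standardized effect.

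**What to change.** 1. State how time was scored. If it was 0/1, correct the Sample size text. If it was weeks, rescale the slope variance: 0.10 over the whole interval is 0.10/256 = 0.0004 per week squared.
2. State which SD standardizes the effect.
3. Rerun the simulation with 20% attrition and 10% non-response, and say how each enters.
4. Replace 0.30/0.81 and the 0.25 at N = 468 with the figures obtained. The covariate-adjusted 0.27 and 0.22 come from the same simulation and should be refreshed too.
5. Show the result over a range of residual variances informed by both r and ICC in Table 4, and over slope variances such as 0.10 to 0.30.

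The cost is a rerun of an existing simulation and one rewritten paragraph. The stated figure may become less favourable, particularly for the least reliable metrics if individual change varies more than assumed.
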